## Abstract

**Background:**

Endovascular iliac artery interventions rely on the use of two-dimensional digital subtraction angiographies with an iodinated contrast agent and ionizing radiation. The amount of iodinated contrast agent should be limited because of its potentially nephrotoxic effects. Three-dimensional (3D) image fusion requires registration of a preprocedural magnetic resonance angiogram (MRA) or computed tomography (CT) angiogram to a perprocedurally acquired cone-beam CT or two fluoroscopic orthogonal projections. After registration, the 3D angiography images can be overlaid on the fluoroscopy screen and will follow table and C-arm movements. This study will assess the added value of the 3D image fusion technique in iliac artery interventions regarding the amount of the iodinated contrast agent administered.

**Methods/Design:**

The study cohort will comprise 106 patients (> 18 years) with symptomatic common and/or external iliac artery stenoses or occlusions and a recent (< 6 months) diagnostic MRA from the pelvis through the lower extremities, for which an endovascular intervention is indicated. Patients will be randomized into the control or study group (i.e. treatment without or with 3D image fusion guidance). The primary endpoint is the amount of administered iodinated contrast agent (mL). Secondary outcomes are technical success of the procedure, defined as < 30% residual stenosis over the treated lesion, fluoroscopy time, and radiation dose as dose area product (mGycm^2^). Patient participation in the study will be completed after hospital discharge.

**Discussion:**

This study is a randomized controlled multicenter trial to provide evidence on the effect of the 3D image fusion technique on the amount of administered iodinated contrast during endovascular common and/or external iliac artery interventions.

**Trial registration:**

Nederlands Trial Register, NTR5008. Registered on 16 December 2014.

**Electronic supplementary material:**

The online version of this article (10.1186/s13063-018-2981-0) contains supplementary material, which is available to authorized users.

## Background

The iliac arteries are involved in up to 30% of patients with peripheral artery disease (PAD) [1]. The preferred treatment for most patients is endovascular revascularization (i.e. percutaneous transluminal angioplasty [PTA] or recanalization) with optional stent placement. Two-dimensional (2D) digital subtraction angiography (DSA) with iodinated contrast agent and ionizing radiation is the gold standard to visualize the location and severity of the lesion [1]. Because of its potentially nephrotoxic effects, especially in patients with pre-existing renal failure or diabetes mellitus, the amount of iodinated contrast agent should be limited [2, 3].

Non-invasive imaging acquired before the procedure, such as contrast-enhanced magnetic resonance angiography (MRA) or computed tomography angiography (CTA), can be used as guidance during these endovascular interventions. The three-dimensional (3D) image fusion technique is based on the rigid registration of MRA or CTA to a perprocedurally acquired cone-beam computed tomography (CBCT) or, alternatively, two fluoroscopic orthogonal images. This registration is based on bony landmarks, after which the MRA images will be visualized on the 2D fluoroscopy screen (Fig. 1). Because of the registration, the MRA images will follow table and C-arm movements. The 3D image fusion technique does not require the use of additional iodinated contrast agent and has shown to significantly reduce the amount of iodinated contrast agent during endovascular abdominal aortic aneurysm repair (EVAR) [4–8].

**Fig. 1 Fig1:**
[figure not shown]
Example of fluoroscopy with MRA fusion image guidance. **a**, **b** Coronal and sagittal view of the image registration process (the cone-beam CT images in *red* and the MRA images in *blue*). **c** An example of the fusion image guidance during a digital subtraction angiography

No randomized controlled trials have been performed to assess the added value of the 3D image fusion technique in iliac artery interventions so far.

### Hypothesis

The hypothesis of this trial is that the use of the 3D image fusion technique will result in a significant reduction of the amount of administered iodinated contrast agent during endovascular iliac artery interventions compared with the endovascular iliac artery procedures without the use of the 3D image fusion technique.

## Methods/Design

### Study design

This is a prospective randomized, controlled, multicenter trial. The flow diagram of the trial is shown in Fig. 2. The SPIRIT figure can be found in Fig. 3 and the checklist is available in Additional file 1.

**Fig. 2 Fig2:**
[figure not shown]
*Flow diagram* of the trial

**Fig. 3 Fig3:**
[figure not shown]
Schedule of enrolment, interventions, and assessments*

### Study objectives and endpoints

The primary endpoint is the amount of administered iodinated contrast agent (mL). The intra-arterial iodinated contrast agents Ultravist (300 mg/mL; Bayer Vital, Leverkusen, Germany) and Xenetix (300 mg/mL; Guerbet, Roissy, France) will be used during all interventions of the Maastricht University Medical Center (MUMC) and St. Antonius Hospital (SAH), respectively.

Secondary endpoints are the following:Technical success of the procedure, defined as < 30% trans-lesion residual stenosis and no flow-limiting dissections;Fluoroscopy time from the start to end of the procedure in minutes and seconds;Overall procedure time, defined as the time from femoral access to arterial closure (minutes);Radiation dose as dose area product (DAP) in mGycm^2^ from the start to the end of the procedure;Fusion accuracy between the overlaid MRA and DSA, categorized as accurate (< 2 mm), mismatch (2–5 mm), or inaccurate (> 5 mm);Complications that occur during the intervention and before discharge.

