### Intervention

The aim of the endovascular treatment is to obtain a patent CIA and/or EIA (i.e. < 30% residual stenosis or a reduction of the mean pressure gradient to < 10 mmHg [11]), resulting in an improved blood flow to the legs. In case of a flow limiting dissection, > 30% residual stenosis, or acute elastic recoil after PTA, additional stent placement will be performed. If indicated, other arteries will be treated in addition to the CIA and/or EIA during the same intervention. The physician will choose an ipsilateral or contralateral technique (or rendezvous procedure), depending on the location of the lesion. The analysis will not include data of patients with solely diagnostic DSAs.

Before the start of the intervention, the patient will be placed supine on the angiography table. The contrast pump and table contrast agent will be diluted 50:50 with a normal saline solution. For patients randomized into the study group, a non-contrast-enhanced CBCT will be created at the beginning of the intervention using the flat panel detector of the C-arm angiography system (Allura Xper FD20; Philips Healthcare). The CBCT will be automatically transferred to the 3D XtraVision workstation (Philips Healthcare). Subsequently, a manual 3D-3D registration will be performed between the preprocedural MRA and CBCT based on bony landmarks, such as vertebrae and the femoral heads, and the flow lumen on the MRA will be matched to the border of the calcifications as seen on the CBCT. The time required to perform the registration will be recorded.

After the registration, the physician will visually score the fusion accuracy of the entire iliac vasculature between the overlay and the initial DSA run. This fusion accuracy will be determined directly after the DSA is created and will be categorized as accurate (< 2 mm), mismatch (2–5 mm), or inaccurate (> 5 mm). An overlay that is inaccurate will be manually translated or reregistered to achieve a more accurate overlay that will be used during the intervention. Subsequently, the intervention will be performed according to the standard of care procedure and contrast runs will be performed when needed.

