Preoperative MRA or CTA can be used for 3D image guidance. Registration between two similar image modalities (i.e. CTA to CBCT) may be less challenging than registration between MRA and CBCT, because MRA visualizes the flow lumen of the arteries, instead of calcified speculae. Nevertheless, because an MRA of the lower abdomen, pelvis, and lower extremities is the standard diagnostic imaging in the preoperative workflow of many patients with PAD, only patients with preoperative MRA datasets will be included; therefore, patients with contraindications to MRA are not eligible. Furthermore, because of susceptibility artifacts on the MRA, in-stent stenoses cannot be judged and those patients will not be included in this trial. No additional preoperative imaging needs to be performed for this study and patient burden is minimized.

Image registration can be performed to a CBCT (3D-3D image fusion) or two fluoroscopic orthogonal projections (2D-3D image fusion). The acquisition of a CBCT and registration process takes approximately 5–10 min and is reported to be more accurate than 2D-3D image fusion [20]. However, the latter is reported to be fast and can be performed with a minimal effective dose of 0.14–0.20 mSv [21]. Sailer et al. [22] reported that a CBCT corresponds to a mean effective dose of 3.5 mSv (95% confidence interval, 3.0–4.1 mSv), whereas van den Berg [21] reported an effective dose of 1.53–1.66 mSv. The patient’s radiation dose from a CBCT may add 21% of the total procedural DAP for iliac artery interventions [9], which is comparable to approximately 7 min of fluoroscopy time [22]. During fluoroscopy, the physician is at the tableside, but is usually far away from the C-arm during the acquisition of the CBCT. When the 3D fusion technique is used during EVAR, the fluoroscopy time could be significantly reduced [23, 24]. This reduction may also be feasible for iliac artery interventions, which will be beneficial to both the operator and the patient, and could potentially result in a reduction of costs. The possible benefit for contrast saving, combined with the possible reduction of fluoroscopy time might outweigh the additional radiation dose of a CBCT.

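### Overall procedure time starts at femoral access, so the CBCT and registration done only in the study arm can fall outside the clock, and any omission favours fusion

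*Protocol article*

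**What the plan says.** Study objectives and endpoints, in the Protocol article, lists among the secondary endpoints "Overall procedure time, defined as the time from femoral access to arterial closure (minutes"). Two neighbouring endpoints have a different window: "Fluoroscopy time from the start to end of the procedure in minutes and seconds", and dose area product (DAP) "from the start to the end of the procedure".

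The Intervention section first has every patient placed supine on the table, before the intervention starts. It then says: "For patients randomized into the study group, a non-contrast-enhanced CBCT will be created at the beginning of the intervention". The scan goes to a workstation, where it is registered by hand to the MRA using bony landmarks and calcifications. The section adds that "The time required to perform the registration will be recorded". The physician then scores the overlay against the initial DSA run.

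The Discussion gives the duration: "The acquisition of a CBCT and registration process takes approximately 5–10 min". No section states whether femoral access is obtained before or after the CBCT.

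**The concern.** The CBCT uses no contrast, and the registration as described needs no catheter. Both could therefore be finished before the artery is punctured. The first described step that does need access is the initial DSA run. An endpoint called overall procedure time can thus leave out a step that exists in one arm only, and whether it does depends on how the operator orders the work.

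Any omission can run in one direction only, in favour of fusion. The trial is unblinded and runs at two sites, so the order may differ between operators or sites. The clock may also treat like steps unequally: an initial registration done before access would not count, whereas a re-registration prompted by a poor match on the initial DSA would.

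At stake is the reading of one secondary endpoint. A shorter access-to-closure time could be reported as time saved when the work had only moved to before the puncture.

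**Working it through.** **Inputs from the Protocol article**
- Patients per group: 48 (Sample size calculation and statistical analysis).
- Test: two-sided, 0.05, independent-samples t-test if the data are normal (same section).
- CBCT plus registration: about 5–10 min, study arm only (Discussion; Intervention).

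**Input assumed**
- SD of procedure time: not in the documents; taken as 20, 30 and 40 min.

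**The plan's own figure.** There is none for procedure time. The group size reproduces from the contrast endpoint: N > 4 × (3.24 × 30 / 20)² = 94.5. A two-sided calculation for a 20 mL difference with SD 30 mL and 90% power gives 48 per arm, 96 in total, as stated. Adding 10% gives 96 × 1.10 = 105.6, the planned 106. The present point does not touch these numbers.

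**Size of a full omission.** Suppose true total time (set-up included) is equal in the two arms, and every study patient has the whole set-up before access. The measured difference is then −δ, with δ the omitted time. The standard error is SE = SD × √(2/48):
- SD 20: SE = 4.08 min
- SD 30: SE = 6.12 min
- SD 40: SE = 8.16 min

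The noncentrality is δ/SE, for example 10/4.08 = 2.45 and 5/8.16 = 0.61. The noncentral t distribution with 94 degrees of freedom (critical value 1.986) gives the chance of a significant result favouring fusion:

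| Assumed SD | δ = 5 min | δ = 7.5 min | δ = 10 min |
|---|---|---|---|
| 20 min | 23% | 44% | 68% |
| 30 min | 12% | 23% | 37% |
| 40 min | 9% | 15% | 23% |

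Without the omission, the chance in that direction is 2.5%.

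**Mixed sequence.** If only half of the study patients have the set-up before access, the mean omission is halved. Ignoring the small extra spread that mixing adds, a 10 min set-up then acts like δ = 5: at SD 20 the chance falls from 68% to 23%. If access always comes first, the omission and the bias are zero.

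**The case against.** **The order is not stated, so the bias is not shown.** This is right, and it limits the point. A reader might infer that the comparison is certainly biased. The article does not support that: it places the CBCT at the beginning of the intervention, and access may already have been obtained. What stands is that the endpoint's content depends on a sequence that the protocol leaves open.

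**Access to closure is explicit and identical in both arms.** Also right, and it is a legitimate measure of time with an artery open. It is not an overall time when one arm may do extra work before it begins.

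**Registration time is recorded.** It is, which allows a partial correction. It is not a listed endpoint, no stated rule adds it to procedure time, and the article mentions recording neither CBCT acquisition time nor its order relative to access. Further detail may stand in the full protocol, but the definition printed here is fixed and would still need changing or supplementing.

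**The percentages rest on an assumed SD and a worst case.** They do. They illustrate scale and do not predict a result.

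**DAP.** A reader might infer that DAP has the same weakness and that the CBCT dose can drop out. The documents do not support this. The DAP window is not tied to femoral access; that anchor belongs to the procedure-time endpoint alone. The Intervention section places the CBCT within the intervention, and the Discussion counts its dose as procedural: "The patient’s radiation dose from a CBCT may add 21% of the total procedural DAP for iliac artery interventions". The start of the procedure is not spelled out for DAP, but the CBCT appears meant to be counted.

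**Conclusion.** The point holds for overall procedure time, as a conditional weakness in one secondary endpoint. The stated clock can leave out up to 5–10 min of work done only in the study arm, and any omission favours fusion. The chance of a falsely significant saving would be about 9% (5 min, SD 40) to 68% (10 min, SD 20). That range assumes equal true total times, 48 per arm, the full omission in every study patient, and an SD that is not in the documents. It is smaller with a mixed sequence and disappears if access always precedes the CBCT.

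The DAP definition is not an error. The primary endpoint (contrast volume) and the sample size are unaffected. The change is worth making because it is cheap and the Trial status section reports only 40 of the 106 patients enrolled.

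**What to change.** - Start the clock for overall procedure time in both arms at one event that precedes the CBCT, and end it at arterial closure. Positioning on the table is suitable, since the Intervention section already describes it for all patients.
- Keep access-to-closure as a supporting measure under a name that says what it covers.
- For patients already enrolled, report a sensitivity analysis that adds the recorded registration time where it preceded access, and the CBCT time if available. Say plainly that the correction is partial where CBCT time or the order of steps was not captured.
- Optionally, add a phrase stating that DAP includes all CBCT exposures. This is a clarification only.

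The cost is a reworded endpoint definition, one extra time stamp on the eCRF, and a time result that may look less favourable to fusion.

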### Patients

The study cohort will comprise 106 patients (> 18 years) with symptomatic common iliac artery (CIA) and/or external iliac artery (EIA) stenoses or occlusions and Rutherford category 1–6, a recent (< 6 months) diagnostic MRA from the pelvis through the lower extremities, and an indication of endovascular intervention (PTA or recanalization). Participants will be randomized 1:1 to the control or study group (i.e. standard PTA or recanalization with or without the 3D image fusion technique). Patients will be included from the MUMC and SAH. Inclusion and exclusion criteria are summarized in Table 1.

**Table 1 Tab1:** Eligibility criteria

Inclusion	Exclusion
Patients with PAD of the CIA and/or EIA for which an endovascular intervention is indicated	Age < 18 years
Rutherford class 1–6	Treatment for acute arterial ischemia
A recent (< 6 months) diagnostic MRA from the pelvis through the lower extremities with sufficient quality without artifacts (e.g. in stent restenosis or patient movement)	Allergy for iodinated contrast agents
Signed informed consent	Patients with aneurismal lesions of the iliac artery
	Pregnancy or breast-feeding

### Randomization

Randomization will be performed by the investigators with the use of an automated web-based randomization and electronic data capture software (MACRO 4.6.0, https://ecrf.ctcm.nl/macro). Randomization will be performed according to minimization; for a difference of 2 between the two groups (control and study group), there is a 90% chance that the next individual will be allocated to the group with the smallest number of patients. Stratification factors are the site (MUMC or SAH), weight (≤ 90 or > 90 kg), and estimated glomerular filtration rate (eGFR) (≤ 60 or > 60 mL/min/1.73m^2^). It is expected that the site, weight and eGFR have the biggest impact on the outcome measures. First, the groups should be similar regarding renal function because this may affect outcome. It can be argued that in patients with a reduced renal function, physicians are more careful with the amount of administered contrast. Thus, by using the eGFR as a stratification factor, this bias will be minimized. Second, the radiation dose is taken into account, which is dependent on the patients’ weight. Therefore, stratification on weight is important. Third, it is not preferable to have one of the sites primarily performing the interventions with the 3D fusion technique and vice versa, since that would influence the user experience and is possibly also be related to the amount of contrast volume that is administered and the radiation dose that is used. Hence, these stratification factors were chosen to keep the distribution between the groups equal. Owing to the nature of the study, randomization will not be blinded for patients or physicians.

### Ethics

The study will be conducted in accordance with the principles of the Declaration of Helsinki and the Medical Research Involving Human Subjects Act (in Dutch: Wet Medisch Wetenschappelijk Onderzoek met Mensen). The local medical ethical committees of both hospitals have approved the study protocol (NL47680.068.14, version 1.4). The study protocol was registered at the Netherlands Trial Register at www.trialregister.nl on 16 December 2014 (registration number: NTR5008). All patients will give written informed consent before study inclusion and randomization. Patient participation is voluntary; the participant can request to stop participation to the study at any time.

### Sample size calculation and statistical analysis

The sample size was calculated using a two-tailed t-test with null hypothesis *E(D) = 0* (no difference between the groups) and alternative hypothesis *E(D) ≠ 0* (groups are different). A type I error (*α*) of *0.05* with z-value *Z*_*α*_ ≈ *1.96* was accepted resulting in1$$ {Z}_{\alpha }=\sqrt{N}\frac{D}{\sigma_D}>1.96 $$with *N* the sample size and *σ*_*D*_ the expected standard deviation. When assuming the alternative hypothesis is true *E(D) = τ* the power (*π*(*τ*)) can be calculated by2$$ \pi \left(\tau \right)=1-\Phi \left(1.96-\sqrt{N}\frac{\tau }{\sigma_D}\right) $$with Φ being the Phi coefficient. When accepting a power of at least 0.90, the alternative hypothesis for *E(D) = τ* can be estimated by

3$$ \pi \left(\tau \right)=1-\Phi \left(1.96-\sqrt{N}\frac{\tau }{\sigma_D}\right)>0.90. $$

Alternatively, this can be written with as4$$ \Phi \left(1.96-\sqrt{N}\frac{\tau }{\sigma_D}\right)<0.10. $$

For a type II error of 0.1, the z-value (*Z*_*β*_) becomes approximately *1.28*5$$ \sqrt{N}\frac{\tau }{\sigma_D}>1.96+{Z}_{\beta }=1.96+1.28\approx 3.24 $$

Given that half of the proportion of the study patients is randomized into the control group (*q*_0_ = 0.5) and the other half in the study group (*q*_1_ = 1 − *q*_0_ = 0.5), the sample size (*N*) can then be estimated by6$$ N>\left(\frac{1}{q_0}+\frac{1}{q_1}\right){\left(\frac{3.24}{\tau }{\sigma}_D\right)}^2 $$

Based on earlier research [9], we expect that *τ* = 20 mL of administered contrast volume may be reduced with the use of the 3D image fusion technique by reducing the number of contrast runs by at least two. Full-strength iodinated contrast is diluted 50:50 with a normal saline solution because a lower concentration of iodinated contrast agent has been shown not to compromise image quality during DSA of PAD patients [10]. To achieve a reduction of 20 mL per procedure with a mean volume of 60 mL and corresponding standard deviation of *σ*_*D*_ = 30 mL, the sample size *N* becomes a total of 96 patients. Therefore, 48 patients will be needed in each group. Adjusting for an anticipated loss to follow-up of 10%, the total sample size will be 106 patients. An interim analysis will be performed halfway through, after inclusion of the first 40 patients, to assess the efficacy of the 3D fusion technique compared to the control group.

Normal distribution of the data will be tested. Normally distributed data will be represented as the mean and 95% confidence interval; non-normally distributed data will be represented as the median and interquartile range. Continuous variables will be analyzed with the independent samples *t*-test or Mann–Whitney *U* test for normally and non-normally distributed data, respectively. Categorical data will be analyzed with the *χ*^2^ test. All tests will be two-sided and considered significant when *P* < 0.05.

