### Monitoring and adverse events

A Data and Safety Monitoring Board (DSMB) will not be appointed for this study. A qualified monitor of the Clinical Trial Center Maastricht (CTCM) will monitor the study, which will ensure that the study is conducted according to ICH-GCP guidelines. Visits are conducted at the start of the study, after inclusion of five patients, halfway through, and at completion of the study. A monitoring report will be sent to the investigator after each visit.

Adverse events and serious adverse events will be recorded on the eCRFs. They will comprise a description of the event, type of complication (i.e. access site, systemic, organ-specific), severity, start date, end date, whether suspected to be intervention related, any action that is undertaken, and the outcome. Serious adverse events will be reported to the accredited METC through the “Toetsingsonline” page of the website of the Central Committee on Research Involving Human Subjects (in Dutch: Centrale Commissie Mensgebonden Onderzoek, CCMO [www.ccmo.nl]). The investigator will report serious adverse device events resulting from the use of the 3D image fusion technique to the accredited METC, the manufacturer, and the Inspection for Healthcare (in Dutch: Inspectie voor Gezondheidszorg [IGZ]).

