### Trial status

The METC has approved the study protocol. Currently, 40 patients have been enrolled in the 3DMR-Iliac-Roadmapping study. The expected project completion for this trial is December 2018.

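### The efficacy interim at 40 patients falls under the same unadjusted P < 0.05 as the final test; if a significant result at either look counts, the overall type I error is about 8.6–8.7%, not 5%

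*Protocol article*

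**What the plan says.** All but two of the relevant statements stand in the protocol article, section *Sample size calculation and statistical analysis*.

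- Error rate: "A type I error (*α*) of *0.05* with z-value" of about 1.96 is accepted. "The sample size was calculated using a two-tailed t-test", with 90% power, a 20 mL reduction and an SD of 30 mL. This gives 96 patients, or 106 after allowing for 10% loss.
- Interim: "An interim analysis will be performed halfway through, after inclusion of the first 40 patients, to assess the efficacy of the 3D fusion technique", in comparison with the control group.
- Significance rule, closing the same section: "All tests will be two-sided and considered significant when *P* < 0.05". No exception is made for the interim.

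The article gives no interim boundary, no alpha spending, no adjusted final level, no stopping consequence, and no statement that the interim is descriptive only.

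Under *Monitoring and adverse events*: "A Data and Safety Monitoring Board (DSMB) will not be appointed for this study". Under *Trial status*: "Currently, 40 patients have been enrolled in the 3DMR-Iliac-Roadmapping study". The trigger for the interim had therefore been reached when the article was written.

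**The concern.** An interim analysis that assesses efficacy is a test of the primary hypothesis. The only significance level the article gives applies to all tests. Followed as written, the primary comparison is made twice at 0.05, while the sample size and the stated error rate allow for one comparison. Two chances of a false positive at 0.05 each give more than 0.05 overall.

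Two further things depend on how the interim is used. If the trial stopped on a nominally significant result with about 20 patients per arm, the reported contrast saving would tend to be too large, because only the larger observed differences pass the threshold at that size. And any boundary that depends on the information fraction needs the correct fraction, whereas the article gives two that disagree: *halfway*, and 40 patients.

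**Working it through.** **Inputs.** From the sample size section: two-sided alpha 0.05 (z = 1.96), power 0.90, effect 20 mL, SD 30 mL, 96 evaluable and 106 total, interim after 40. From *Patients*: 1:1 allocation. Assumption: about 20 patients per arm at the interim, all with data.

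**1. The plan's own figure.** Equation 6 gives 4 × (3.24 × 30/20)² = 94.5, which is 48 per arm after rounding up, or 96. Power with 48 per arm is 0.904. Then 96 × 1.1 ≈ 106. The sample size is thus reproduced as a single-look design, with no allowance for the interim.

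**2. Timing.** 40/106 = 37.7% and 40/96 = 41.7%. Half would be 53 or 48. Forty is half of 80, a total that appears nowhere in the article.

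**3. Overall type I error with P < 0.05 at both looks.** Under the null, the interim and final statistics are bivariate normal with correlation √t, where t is the information fraction. The overall error is 1 − P(|Z₁| < 1.96 and |Z₂| < 1.96).

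| Interim / final | t | √t | Overall error | Simulated t-tests (200,000 runs) |
|---|---|---|---|---|
| 40 / 96 | 0.417 | 0.645 | 0.0858 | 0.0856 |
| 40 / 106 | 0.377 | 0.614 | 0.0870 | 0.0874 |
| true half | 0.500 | 0.707 | 0.0831 | not run |

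The unadjusted second look accounts for nearly all of the excess. Looking at 40 patients and not at the true half adds 0.0858 − 0.0831 = 0.0027 to 0.0870 − 0.0831 = 0.0039, or 0.3–0.4 percentage points.

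**4. What an interim P < 0.05 would mean under the planned effect.** The standard error at 20 per arm is 30 × √(2/20) = 9.49 mL, so the mean of Z₁ is 20/9.49 = 2.11. P(Z₁ > 1.96) = 0.56 (0.54 with the t distribution). Given Z₁ > 1.96, the mean observed saving is 9.49 × [2.108 + φ(1.96 − 2.108)/0.559] = 9.49 × 2.814 = 26.7 mL, about one third above the true 20 mL.

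**5. Boundaries that hold the error.**

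| Rule | Interim P | Final P | Overall error |
|---|---|---|---|
| Haybittle–Peto, t = 0.417 | 0.001 | 0.05 | 0.0503 |
| Haybittle–Peto, t = 0.377 | 0.001 | 0.05 | 0.0504 |
| Lan–DeMets O'Brien–Fleming, 0.025 per tail, t = 0.417 | 0.00103 | 0.0497 | 0.05 |
| Lan–DeMets O'Brien–Fleming, 0.025 per tail, t = 0.377 | 0.00053 | 0.0498 | 0.05 |

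The spending convention must be named. If the same function spends the two-sided 0.05 directly, the interim level becomes 0.0024 (t = 0.417) or 0.0014 (t = 0.377), with final levels of 0.0490 and 0.0494. Both conventions are valid, but they differ more than twofold at the interim.

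**6. Cost in power.** With 96 patients, the mean of the final Z is 20/(30 × √(2/48)) = 3.266. Power of the final test is Φ(3.266 − 1.960) = 0.904 at 0.05, and Φ(3.266 − 1.963) = 0.904 at 0.0497. The chance of crossing at the interim under the planned effect falls from 0.56 to P(Z₁ > 3.29) = Φ(2.108 − 3.29) = 0.12 with Haybittle–Peto.

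**The case against.** The strongest objection is that the inflation is conditional. The article does not say that the trial may stop, or that an interim P < 0.05 would reject the primary null hypothesis. If only the final test decides, the error stays at 0.05. The step 4 figures go further still, because they need a stopping rule that the article does not contain. This stands, and the conclusion is worded accordingly.

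A second objection is that boundaries normally sit in the full protocol or SAP, which are not shown, and that the all-tests sentence closes a generic paragraph that never mentions the interim. Silence about a boundary would indeed be no finding. But the article is not silent on the level: it fixes 0.05 for every test after planning an efficacy look. If another document sets a boundary, this sentence contradicts it and still needs correcting.

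Three stronger readings are tempting, and the article does not support them.

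- *The trial's error rate is 8.7%.* That holds only if a significant result at either look counts.
- *The mistimed halfway look causes the inflation.* It does not. A look at the true half gives 8.3%, and the trigger itself, 40 patients, is clear.
- *With no DSMB, the unblinded operators will see the interim result and change their use of contrast.* The article does not say who runs or sees the interim. *Data collection* limits each centre to its own eCRF data until the end of the study. That does not rule out circulation of an interim report, but such circulation is not stated.

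**Conclusion.** The point holds in conditional form. The article plans an efficacy interim and applies an unadjusted two-sided 0.05 to all tests. On the plain reading, that a significant result at either look counts as efficacy, the overall type I error is about 8.6% (final N 96) to 8.7% (final N 106), against the 5% stated. This assumes complete data on about 20 patients per arm at the interim; t-test simulation confirms the normal approximation. The overestimate, about 26.7 mL against a true 20 mL, applies only if the trial also stopped on a significant interim result under the planned effect and SD. The sample size of 96 is correct for a single look. The conflict between *halfway* and 40 patients is a separate, minor inconsistency. It matters mainly because a boundary may be calculated from the wrong fraction. Confidence is high in the arithmetic and in the need to change the text. It is lower on whether the inflation would be realised, since the use of the interim result is not stated.

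**What to change.** Before the 40-patient data are opened, choose one of two routes and write it down.

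1. **Non-decisional interim.** State that no efficacy claim or stopping decision will rest on the interim and that only the final test at 0.05 counts, or delete the efficacy look.
2. **A boundary.** Either Haybittle–Peto (interim P < 0.001, final P < 0.05, overall about 0.0504), or Lan–DeMets O'Brien–Fleming with 0.025 spent per tail (interim P < 0.0005 at 40/106 or < 0.001 at 40/96, final about 0.0498 or 0.0497). Name the spending convention and the total on which the fraction is based.

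On either route, exempt the interim from the sentence that puts all tests at 0.05, and replace the *halfway* wording with: after 40 of 106 patients (38%). As a precaution, state who will run the interim and keep the comparison from the treating operators.

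This costs one or two sentences. Power is practically unchanged, at 0.904 before and after. The real price is a smaller chance of an early efficacy claim: about 0.12 with Haybittle–Peto under the planned effect, against 0.56 at an unadjusted 0.05.
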